# Migraine and risk of premature myocardial infarction and stroke among men and women: A Danish Population-based cohort study. Statistical analysis plan

## Aim

To examine the impact of migraine on the association between sex and risk of premature stroke and myocardial infarction

*March 2023:*

*We originally intended this to be a study of interaction between migraine and sex on risk of premature myocardial infarction and stroke. However, it did not seem obvious who were going to be the exposed sex and therefore we changed the study aim to be one of effect modification, i.e. what was the impact of migraine among men and among women. The title was changed accordingly.*

## METHODS

## Setting and design

We will perform a population-based cohort study in Denmark using data obtained from national registries. Individual level data will be linked using the 10-digit civil registration number issued by the Civil Registration system. The source population will be all Danish residents during the period of 1 January 1996 through 31 December 2016.

## Data Sources

The Civil Registration System, CRS

The Danish National Patient Registry, DNPR

The Danish National Prescription Registry, NPR

The Danish Registry of Causes of Death, DRCD

The Danish Integrated Database for Labor Market Research, IDA

The Psychiatric Central Registry, PCR

The Danish Stroke Registry, DSR

## Study cohorts

**MIGRAINE ICD DIAGNOSIS study**

**Migraine cohort:** All patients aged 18-60 with a first-time primary or secondary diagnosis of migraine (inpatient, outpatient, and emergency room diagnoses) recorded in the DNPR during the study period. Index date will be date of diagnosis (admission date). Patients with a diagnosis of stroke or MI (inpatient/outpatient only) recorded in the DNPR before index date or with a diagnosis of migraine prior to the study period will be excluded.

**General population comparison cohort:** From the CRS we will randomly sample 10 comparison cohort members for each migraine patient. Comparison cohort members will be matched on birth year and year of index date. Matching will be done with replacement. They will be assigned the index date corresponding to that of their matched migraine patient. Individuals are eligible for the comparison cohort if they are alive on the index date, have no previous diagnosis of stroke, MI or migraine before the index date.

If a member of the comparison cohort receive a diagnosis of migraine during follow-up, the individual joins the migraine cohort.

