**PRESCRIPTIONS study**

**Migraine prescription cohort:** All patients aged 18-60 with at least two redeemed prescriptions for migraine specific medication recorded in the NPR (available from 1995) during the study period. Index date will be date of redemption of second prescription. Patients with a diagnosis of stroke or MI (in/outpatient) recorded in the DNPR before index date and patients with two prescriptions before the study period will be excluded.

**General population comparison cohort:** From the CRS we will randomly sample 10 comparison cohort members for each migraine patient. Comparison cohort members will be matched on birth year and year of index date. Matching will be done with replacement. They will be assigned the index date corresponding to that of their matched migraine patient. Individuals are eligible for the comparison cohort if they are alive on the index date, have no previous diagnosis of stroke, MI, and have not redeemed 2 or more prescriptions of migraine specific medication before the index date.

If a member of the comparison cohort receives two prescriptions of migraine specific medications during follow-up, the individual joins the migraine cohort.

*March 2023:*

*We initially intended to use the migraine cohorts identified by diagnostic codes in the DNPR as the main analysis. However, seeing, as there were relatively few in this cohort we decided to use this as a sensitivity analysis instead.*

## Exposure 1

Gender

## Exposure 2

Migraine

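### Each study screens its No migraine comparators only on its own migraine definition, so people the linked registries identify as migraine patients can sit in the reference group, mainly in the diagnosis sensitivity analysis

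*SAP*

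**What the plan says.** The SAP defines two parallel cohort studies under Study cohorts.

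- **Diagnosis study.** Exposure is a "first-time primary or secondary diagnosis of migraine (inpatient, outpatient, and emergency room diagnoses) recorded in the DNPR during the study period". Comparators come from the general population ("we will randomly sample 10 comparison cohort members for each migraine patient") and must "have no previous diagnosis of stroke, MI or migraine before the index date". The follow-up rule is: "If a member of the comparison cohort receive a diagnosis of migraine during follow-up, the individual joins the migraine cohort".
- **Prescription study.** Exposure is at least two redemptions of migraine-specific medication. Comparators must "have no previous diagnosis of stroke, MI, and have not redeemed 2 or more prescriptions of migraine specific medication before the index date". The follow-up rule is: "If a member of the comparison cohort receives two prescriptions of migraine specific medications during follow-up, the individual joins the migraine cohort".

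The March 2023 note after the prescription study reverses the roles of the two studies. The diagnosis cohort had been intended as the main analysis, but "seeing, as there were relatively few in this cohort we decided to use this as a sensitivity analysis instead".

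Three other places bear on the point:

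- Data Sources lists both the DNPR and the NPR, and Setting and design says that individual-level data are linked.
- Table A1 has a single Migraine exposure row, sourced from both registries, with ICD and ATC codes side by side.
- Tables 1 and 2 label the comparison group No migraine.

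**The concern.** Each study removes from its comparators only the kind of migraine that it uses to define exposure. A person with many redemptions but no hospital diagnosis is exposed in the main analysis, yet eligible as unexposed in the sensitivity analysis. A person with a hospital diagnosis and fewer than two redemptions can be unexposed in the main analysis. The gap exists at entry and continues through follow-up.

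Exposed people in the reference group raise its event rate, if migraine raises risk, and so pull the migraine hazard ratio towards 1. Two uses of the results are affected. First, the diagnosis study serves as a check on the main result, and part of any difference between the two could come from differently composed reference groups. Second, the revised aim is the impact of migraine among men and among women. If the affected share differs by sex, the two sex-specific hazard ratios are diluted by different amounts.

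**Working it through.** **Step 1: set the rules side by side.**

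| Rule for comparators | Diagnosis study (sensitivity) | Prescription study (main) |
|---|---|---|
| Prior DNPR migraine diagnosis excludes | Yes | No |
| Two or more prior NPR redemptions exclude | No | Yes |
| New diagnosis in follow-up moves the person | Yes | No |
| Second redemption in follow-up moves the person | No | Yes |

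No text in the SAP closes the cells marked No. Table A1 lists both code sets under one exposure but does not say that comparators must be free of both.

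**Step 2: dilution formula.** The SAP states no effect size, event count or migraine prevalence, so there is no figure of its own to reproduce. Let q be the share of comparator person-time contributed by people who meet the other definition. Assume they have the same hazard ratio (HR) as the exposed cohort. Then

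observed HR = HR / [(1 − q) + q × HR] = HR / [1 + q(HR − 1)].

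**Step 3: diagnosis study.** All values of q and HR are assumptions.

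| True HR | q = 3% | q = 5% | q = 10% |
|---|---|---|---|
| 1.2 | 1.193 | 1.188 | 1.176 |
| 1.5 | 1.478 | 1.463 | 1.429 |
| 2.0 | 1.942 | 1.905 | 1.818 |

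For example, 1.5 / (1 + 0.10 × 0.5) = 1.5 / 1.05 = 1.429. At HR 1.5 the excess lost is (1.5 − 1.478) / 0.5 = 4% at q = 3%, and (1.5 − 1.429) / 0.5 = 14% at q = 10%.

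**Step 4: prescription study.** The affected people have a hospital diagnosis and fewer than two redemptions. Because the SAP reports relatively few diagnosed patients, q should be small. At HR 1.5, q = 0.5% gives 1.496 and q = 1% gives 1.493.

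**Step 5: unequal shares by sex.** Assume a true HR of 1.5 in both sexes, q = 10% in one sex and 4% in the other. The observed HRs are 1.5 / 1.05 = 1.429 and 1.5 / 1.02 = 1.471. Now give the 10% to women and assume that men's baseline rate is twice women's. The four rates, relative to women truly free of migraine, are 1.05 (women, comparators), 1.5 (women, migraine), 2.04 (men, comparators) and 3.0 (men, migraine). RERI is (3.0 − 2.04 − 1.5 + 1.05) / 1.05 = 0.486, against 0.50 without contamination.

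**Step 6: the equal-HR assumption.** If the affected comparators have their own hazard ratio HRc, the denominator becomes 1 + q(HRc − 1). With HRc = 1.2, true HR 1.5 and q = 10%, the observed HR is 1.5 / 1.02 = 1.471 rather than 1.429. With HRc = 1 there is no dilution.

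**The case against.** Within each study, one definition governs exposure, exclusion and change of cohort, which is internally consistent, and both groups are called general population cohorts. Two redemptions are also only a proxy for migraine: Table A1 counts two codes (N02CX01-02) that it marks as prophylaxis. The defect falls mainly on what is now a sensitivity analysis.

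Part of this stands. The proxy argument bears on size, but it is a weak reason for keeping such people as comparators, because the same two redemptions define the main exposed cohort. The general-population label does not settle the matter either, since each study already removes its own kind of migraine and the tables call the remainder No migraine. The limited reach of the defect is a fair point and is reflected in the weight given here.

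A reader might infer more than the SAP supports:

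- **That a weaker result in the diagnosis study could be contamination alone.** Over the assumed range only a small gap can be explained. For a true HR of 1.5 to appear as 1.2, q would have to be (1.5 / 1.2 − 1) / 0.5 = 50%.
- **That the reference group holds most identifiable migraine patients.** The March 2023 note gives no counts, and eligibility is not composition. Comparators are a random sample of the matched population, so q is that population's share with two or more redemptions and no diagnosis. The SAP does not report this share.
- **That women's results are diluted more.** The SAP gives no sex split of migraine or its treatment. The assignment of the 10% to women in the working is illustrative only.

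**Conclusion.** The point holds as a modest, avoidable misclassification caused by the stated eligibility and switching rules. It biases the migraine hazard ratio towards 1. Under assumed shares of 3% to 10% and an equal hazard ratio, a true 1.5 becomes 1.48 to 1.43 in the diagnosis study. In the main prescription analysis, a share of 1% or less changes it by less than 0.01. A modest part of any weaker association in the sensitivity analysis could therefore reflect its reference group. If the shares differ by sex, the sex-specific hazard ratios are diluted unequally, in a direction that the SAP does not allow one to state.

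The SAP does not support a claim that the main result is seriously compromised. The absence of a both-definitions exclusion is certain from the text. The size is not: it rests on the assumed q, on the equal-HR assumption and, for the main analysis, on the remark that diagnosed patients were few.

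**What to change.** In both studies:

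1. Require comparators to have, before the index date, neither a DNPR migraine diagnosis nor two or more NPR redemptions of migraine-specific medication.
2. During follow-up, keep the existing move to the migraine cohort when the study's own definition is met. Censor comparators when the other definition is first met, and add this to the end-of-follow-up list in Statistical analysis, item 2.
3. Report by sex the number of comparators removed or censored under the new rule, so that q is known rather than assumed.
4. Align the single Migraine row in Table A1 with the two cohort definitions.

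The cost is one or two sentences per study and a filter or re-draw. Filtering at q = 10% leaves on average 10 × 0.9 = 9 comparators per patient. Near the null, the variance of the log hazard ratio is roughly proportional to 1 + 1/m for m comparators, so it rises by (1 + 1/9) / (1 + 1/10) = 1.111 / 1.100, about 1%. A re-draw avoids even this, from a slightly smaller pool.

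Two limits should be stated. NPR data are available only from 1995, so the redemption look-back is about one year for 1996 index dates and over 20 years by the end of 2016; early comparators will be screened less completely. The March 2023 notes also show that cohort sizes had already been seen, so the change should be dated and explained in the same way as the other amendments.

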**PRESCRIPTIONS study**

**Migraine prescription cohort:** All patients aged 18-60 with at least two redeemed prescriptions for migraine specific medication recorded in the NPR (available from 1995) during the study period. Index date will be date of redemption of second prescription. Patients with a diagnosis of stroke or MI (in/outpatient) recorded in the DNPR before index date and patients with two prescriptions before the study period will be excluded.

**General population comparison cohort:** From the CRS we will randomly sample 10 comparison cohort members for each migraine patient. Comparison cohort members will be matched on birth year and year of index date. Matching will be done with replacement. They will be assigned the index date corresponding to that of their matched migraine patient. Individuals are eligible for the comparison cohort if they are alive on the index date, have no previous diagnosis of stroke, MI, and have not redeemed 2 or more prescriptions of migraine specific medication before the index date.

If a member of the comparison cohort receives two prescriptions of migraine specific medications during follow-up, the individual joins the migraine cohort.

*March 2023:*

*We initially intended to use the migraine cohorts identified by diagnostic codes in the DNPR as the main analysis. However, seeing, as there were relatively few in this cohort we decided to use this as a sensitivity analysis instead.*

## Exposure 1

Gender

## Exposure 2

Migraine

## Outcome

The primary outcome will be occurrence of premature stroke or MI (IN/OUT, A/B diagnoses) (i.e. before the age of 61) recorded in the DNPR.

*March 2023:*

*To increase the validity of the outcome diagnoses we decided to only include inpatient codes. Furthermore, we decided to do separate analyses for ischemic stroke and hemorrhagic stroke.*

## Covariables

Charlson comorbidity index (excluding MI and cerebrovascular disease) (A/B diagnoses, IN/OUT/ED)

CCI score (low, medium, high) (excluding MI and cerebrovascular disease)

Other comorbidities (see Table 1) (A/B diagnoses, IN/OUT/ED)

Socioeconomic status (highest level of education, income and employment status)

Tables of definitions of covariables can be found in the appendix table A2.

*March 2023:*

*Data regarding employment status were incomplete from 2014 and forth, and therefore we did not include this information. We included ever-redeemed prescriptions to the descriptive tables.*

## Tables

| **Table 1**  **Baseline characteristics according to gender and migraine status** | | | | |
| --- | --- | --- | --- | --- |
|  | **Women** | | **Men** | |
|  | **No migraine**  **n (%)** | **Migraine**  **n (%)** | **No migraine**  **n (%)** | **Migraine**  **n (%)** |
| **All** |  |  |  |  |
| **Aura** | | | | |
| Yes | - |  | - |  |
| No | - |  | - |  |
| Unknown | - |  | - |  |
| Presciption-based |  |  |  |  |
| **Age, median (IQR)** |  |  |  |  |
| **Calendar period at index date** | | | | |
| 1978-1987 |  |  |  |  |
| 1988-1997 |  |  |  |  |
| 1998-2007 |  |  |  |  |
| 2008-2018 |  |  |  |  |
| **Highest level of education** | | | | |
| Low |  |  |  |  |
| Medium |  |  |  |  |
| High |  |  |  |  |
| Unknown |  |  |  |  |
| **Charlson Comorbidity Index** | | | | |
| Low |  |  |  |  |
| Medium |  |  |  |  |
| High |  |  |  |  |
| **Individual Charlson Comorbidities** | | | | |
| Heart failure |  |  |  |  |
| Peripheral vascular disease |  |  |  |  |
| Dementia |  |  |  |  |
| Chronic pulmonary disease |  |  |  |  |
| Connective tissue disease |  |  |  |  |
| Ulcer disease |  |  |  |  |
| Mild liver disease |  |  |  |  |
| Diabetes |  |  |  |  |
| Hemiplegia |  |  |  |  |
| Moderate to severe renal disease |  |  |  |  |
| Diabetes with end organ failure |  |  |  |  |
| Tumor |  |  |  |  |
| Leukemia |  |  |  |  |
| Lymphoma |  |  |  |  |
| Moderate to severe liver disease |  |  |  |  |
| Metastatic solid tumor |  |  |  |  |
| AIDS |  |  |  |  |
| **Other comorbidities** | | | | |
| Hypertension |  |  |  |  |
| Atrial fibrillation or flutter |  |  |  |  |
| Hyperlipidemia |  |  |  |  |
| Atherosclerosis |  |  |  |  |
| Pulmonary embolism |  |  |  |  |
| Deep vein thrombosis |  |  |  |  |
| Valvular heart disease |  |  |  |  |
| Obesity |  |  |  |  |
| Thyroid disease |  |  |  |  |
| Other alcoholism related disease |  |  |  |  |
| Psychiatric disease |  |  |  |  |
|  |  |  |  |  |

| **Table 2**  **Cumulative incidence and hazard ratios of myocardial infarction (MI) according to gender and migraine-status** | | | | | | | | | |
| --- | --- | --- | --- | --- | --- | --- | --- | --- | --- |
| **Gender** | **Migraine-status** | **Total**  **N** | **Stroke or MI**  **N** | **Peron years**  **Y** | **Cumulative incidence**  **(95% CI)** | **Adjusted HR***  **(95% CI)** | **Interaction** | | |
|  |  |  |  |  |  |  | **Interaction contrast** | **Attributable fraction** | **Relative excess risk due to interaction** |
| All | No migraine |  |  |  |  | Reference | - | - | - |
| All | Migraine |  |  |  |  |  | - | - | - |
| Women | No migraine |  |  |  |  | Reference | Reference | Reference | Reference |
| Women | Migraine |  |  |  |  |  |  |  |  |
| Men | No migraine |  |  |  |  | Reference |  |  |  |
| Men | Migraine |  |  |  |  |  |  |  |  |
| *Adjusted for socioeconomic status and comorbidities | | | | | | | | | |

## Appendix

| **Table A1: Definition of exposures and outcome** | | | | | | | |
| --- | --- | --- | --- | --- | --- | --- | --- |
| **Role in the analysis** | **Variable** | **Data sources** | **Categories** | **ICD8-codes** | **ICD10-codes** | **ATC-codes** | **Notes** |
| **Exposure 1** | **Gender** | CRS | Male  Female |  |  |  |  |
| **Exposure 2** | **Migraine** | DNPR  NPR |  | 346.00  346.08  346.09 | G43.0-43.3  G43.8  G43.9 | N02CC, N02CA01-02,  N02CA04, N02CA52  N02CX01-02 | At least two redemptions.  N02CX01-02 are prophylaxis |
|  | Migraine with aura | DNPR |  | - | G43.1 |  |  |
|  | Migraine without aura | DNPR |  | 346.00  346.08  346.09 | G43.0 |  |  |
| **Outcome** | **Stroke** | DNPR |  | 430, 431,433, 434 | I60, I61,  I63, I64 |  |  |
|  | Ischemic stroke | DNPR |  | 433-434 | I63 |  |  |
|  | Subarachnoid hemorrhage | DNPR |  | 430 | I60 |  |  |
|  | Intracerebral hemorrhage | DNPR |  | 431 | I61 |  |  |
|  | Not specified | DNPR |  | - | I64 |  |  |
|  | **Myocardial infarction** | DNPR |  | 410 | I21 |  |  |
|  | STEMI | DNPR |  |  | I21.0-I21.3 |  |  |
|  | Non-STEMI | DNPR |  |  | I21.4 |  |  |
|  | Unspecified | DNPR |  |  | I21.9 |  |  |

| **Table A2: Definitions of covariables** | | | | | | |
| --- | --- | --- | --- | --- | --- | --- |
| **Variable** | **Data sources** | **Categories** | **ICD8-codes** | **ICD10-codes** | **ATC-codes** | **Notes** |
| Birth year (matched on) | CRS |  |  |  |  |  |
| Socioeconomic status  Highest level of education | IDA | Low (primary or lower secondary)  Medium (upper secondary or academic profession degree)  High (University education at bachelor degrees or higher) or missing |  |  |  |  |
| Socioeconomic status  Income | IDA | Low, medium, high, very high, missing |  |  |  | Based on average of 5 previous years of income. Categories according to percentiles from year previous to index date. If one of income is missing based on average of 4 other years |
| Socioeconomic status  Employment | IDA | Employed, unemployed, early retirement, state pension, under education or missing |  |  |  | Year closest to index year within 5 years up to index year |
| **Charlson comorbidity Index** |  |  |  |  |  |  |
| Heart failure | DNPR |  | 427.09; 427.10; 427.11; 427.19; 428.99; 782.49 | I50; I11.0; I13.0; I13.2 |  | Score: 1 |
| Peripheral vascular disease | DNPR |  | 440; 441; 442; 443; 444; 445 | I70; I71; I72; I73; I74; I77 |  | Score: 1 |
| Dementia | DNPR |  | 290.09-290.19; 293.09 | F00-F03; F05.1; G30 |  | Score: 1 |
| Chronic pulmonary disease | DNPR |  | 490-493; 515-518 | J40-J47; J60-J67; J68.4; J70.1;  J70.3; J84.1; J92.0; J96.1; J98.2; J98.3 |  | Score: 1 |
| Connective tissue disease | DNPR |  | 712; 716; 734; 446; 135.99 | M05; M06; M08; M09;M30;M31;  M32; M33; M34; M35; M36; D86 |  | Score: 1 |
| Ulcer disease | DNPR |  | 530.91; 530.98; 531-534 | K22.1; K25-K28 |  | Score: 1 |
| Mild liver disease | DNPR |  | 571; 573.01; 573.04 | B18; K70.0-K70.3; K70.9; K71; K73; K74; K76.0 |  | Score: 1 |
| Diabetes | DNPR |  | 249.00; 249.06; 249.07; 249.09  250.00; 250.06; 250.07; 250.09 | E10.0, E10.1; E10.9  E11.0; E11.1; E11.9 |  | Score: 1 |
| Hemiplegia | DNPR |  | 344 | G81; G82 |  | Score: 2 |
| Moderate to severe renal disease | DNPR |  | 403; 404; 580-583; 584; 590.09; 593.19; 753.10-753.19; 792 | I12; I13; N00-N05; N07; N11; N14; N17-N19; Q61 |  | Score: 2 |
| Diabetes with end organ damage | DNPR |  | 249.01-249.05; 249.08  250.01-250.05; 250.08 | E10.2-E10.8  E11.2-E11.8 |  | Score: 2 |
| Any tumor | DNPR |  | 140-194 | C00-C75 |  | Score: 2 |
| Leukemia | DNPR |  | 204-207 | C91-C95 |  | Score: 2 |
| Lymphoma | DNPR |  | 200-203; 275.59 | C81-C85; C88; C90; C96 |  | Score: 2 |
| Moderate to severe liver disease | DNPR |  | 070.00; 070.02; 070.04; 070.06; 070.08; 573.00; 456.00-456.09 | B15.0; B16.0; B16.2; B19.0; K70.4; K72; K76.6; I85 |  | Score: 3 |
| Metastatic solid tumor | DNPR |  | 195-198; 199 | C76-C80 |  | Score: 6 |
| AIDS | DNPR |  | 079.83 | B21-B24 |  | Score: 6 |
| **Other comorbidities** |  |  |  |  |  |  |
| Hypertension | DNPR  NPR |  | 400-404.99 | I10-I15 | C02A, C02B, C02C, C02DA, C02L, C03A, C03B, C03D, C03E, C03X, C07C, C07D, C08G, C09BA, C09DA, C09XA52, C02DB, C02DD, C02DG, C04, C05, C07, C07F, C08, C09BB, C09DB, C09 | Combination treatment of at least two redeemed prescriptions for different types of drugs within 180 days prior to index date |
| Atrial fibrillation or flutter | DNPR |  | 427.93  427.94 | I48 |  |  |
| Hyperlipidemia | DNPR |  | 272.00, 272.01, 272.08, 272.09 | E78.0-E78.5 |  |  |
| Atherosclerosis | DNPR |  | 440.09, 440.19, 440.20, 440.21, 440.28, 440.29, 440.30, 440.39, 440.99 | I70.0-I70.09 |  |  |
| Pulmonary embolism | DNPR |  | 450.99 | I26 |  |  |
| Deep vein thrombosis | DNPR |  | 451.00 | I80.1-I80.3 |  |  |
| Valvular heart disease | DNPR |  | 394, 395 | I05, I06, I34, I35, I39, I39.1, I51.1A |  |  |
| Obesity | DNPR |  | 277 | E65-E68 |  |  |
| Thyroid disease | DNPR |  | 240-246 | E00-E07 |  |  |
| Other alcoholism related disease | DNPR  NPR |  | 291, 303, 979, 980, 577.10, 571.09, 571.10 | F10 (except F10.0), Z72.1, K86.0, K70, G31.2, G62.1, G72.1, I42.6, K29.2, Z71.4 | Before 31 December 2000: V03AA  After 1 January 2001:  N07BB |  |
| Mood disorder | DNPR |  | 296.x9 (excluding 296.89), 298.09, 298.19, 300.49, 301.19 | F30-F39 |  |  |
| COPD | DNPR |  | 490, 491, 492 | J40, J41, J42, J43, J44 |  |  |
| **Prescriptions** |  |  |  |  |  |  |
| Beta-blockers | NPR |  |  |  | C07 |  |
| ACE-inhibitor/ATII-receptor blocker | NPR |  |  |  | C09A, C09B, C09C, C09D |  |
| Diuretics | NPR |  |  |  | C03 |  |
| Lipid-lowering drugs | NPR |  |  |  | C10 |  |
| Vitamin K antagonists | NPR |  |  |  | B01AA |  |
| NOAC | NPR |  |  |  | B01AE, B01AF |  |
| Clopidogrel | NPR |  |  |  | B01AC04 |  |
| Platelet aggregation inhibitors, excl. clopidogrel and acetylsalicylic acid | NPR |  |  |  | B01AC01-03, B01AC05, B01AC07-56 |  |
| Acetylsalicylic acid | NPR |  |  |  | B01AC06, N02BA01 |  |
| NSAIDs | NPR |  |  |  | M01A |  |
| Combined oral contraceptives | NPR |  |  |  | G03AA, G03AB |  |
| Gestagen only contraceptives, systemic | NPR |  |  |  | G03C |  |
|  |  |  |  |  |  |  |
